### **8.11 Provision of Treatment for Controls**

If this vaccine is proven to be efficacious following analysis of the primary endpoint and if the DSMB agrees, participants allocated to MenACWY group may be offered the IMP, should extra doses become available.

(Protocol V19.0) Following unblinding, control participants aged 30 and above will be offered ChAdOx1 nCoV-19 in the approved MHRA 4-to-12 week, 2-dose schedule (table 14). Participants will remain enrolled in the study and continue the follow up visit schedule listed for their sub-group *concurrently* with the provision of treatment prime and boost visits.

Due to the updated guidance relating to the emerging association of thrombosis with thrombocytopenia and ChAdOx1 nCoV-19, trial participants aged 29 and under will not be offered (prime) vaccinations with ChAdOx1 nCoV-19. These individuals will instead be advised to await vaccination under the national rollout program.

## **9 ASSESSMENT OF SAFETY**

Safety will be assessed by the frequency, incidence and nature of AEs and SAEs arising during the study.

### **9.1 Definitions**

#### **9.1.1 Adverse Event (AE)**

An AE is any untoward medical occurrence in a volunteer, which may occur during or after administration of an IMP and does not necessarily have a causal relationship with the intervention. An AE can therefore be any unfavourable and unintended sign (including any clinically significant abnormal laboratory finding or change from baseline), symptom or disease temporally associated with the study intervention, whether or not considered related to the study intervention.

### 9.1.2 Adverse Reaction (AR)

An AR is any untoward or unintended response to an IMP. This means that a causal relationship between the IMP and an AE is at least a reasonable possibility, i.e., the relationship cannot be ruled out. All cases judged by the reporting medical Investigator as having a reasonable suspected causal relationship to an IMP (i.e. possibly, probably or definitely related to an IMP) will qualify as AR.

Adverse events that may be related to the IMP are listed in the Investigator's Brochure for each product.

### 9.1.3 Serious Adverse Event (SAE)

An SAE is an AE that results in any of the following outcomes, whether or not considered related to the study intervention.

- Death
- Life-threatening event (i.e., the volunteer was, in the view of the Investigator, at immediate risk of death from the event that occurred). This does not include an AE that, if it occurred in a more severe form, might have caused death.
- Persistent or significant disability or incapacity (i.e., substantial disruption of one's ability to carry out normal life functions).
- Hospitalisation or prolongation of existing hospitalisation, regardless of length of stay, even if it is a precautionary measure for continued observation. Hospitalisation (including inpatient or outpatient hospitalisation for an elective procedure) for a pre-existing condition that has not worsened unexpectedly does not constitute a serious AE.
- An important medical event (that may not cause death, be life threatening, or require hospitalisation) that may, based upon appropriate medical judgment, jeopardise the volunteer and/or require medical or surgical intervention to prevent one of the outcomes listed above. Examples of such medical events include allergic reaction requiring intensive treatment in an emergency room or clinic, blood dyscrasias, or convulsions that do not result in inpatient hospitalisation.
- Congenital anomaly or birth defect.

#### **9.1.4 Serious Adverse Reaction (SAR)**

An AE that is both serious and, in the opinion of the reporting Investigator or Sponsors, believed to be possibly, probably or definitely due to an IMP or any other study treatments, based on the information provided.

Reporting of SARs will also apply to concomitant medications, including any other approved or licensed SARS-CoV-2 vaccine, where there is the possibility of an interaction between study interventions and those concomitant medications.

#### **9.1.5 Suspected Unexpected Serious Adverse Reaction (SUSAR)**

A SAR, the nature and severity of which is not consistent with the information about the medicinal product in question set out in the IB.

#### **9.2 Expectedness**

No IMP related SAEs are expected in this study. All SARs will therefore be reported as SUSARs.

#### **9.3 Foreseeable Adverse Reactions:**

The foreseeable ARs following vaccination with ChAdOx1 nCoV-19 include injection site pain, tenderness, erythema, warmth, swelling, induration, pruritus, myalgia, arthralgia, headache, fatigue, fever, feverishness, chills, malaise, nausea and vomiting.

#### **9.4 Adverse Events of Special Interest**

- Disease enhancement following vaccination with ChAdOx1 nCoV-19 will be monitored. Severe COVID-19 disease will be defined using clinical criteria. Detailed clinical parameters will be collected from medical records and aligned with agreed definitions as they emerge. These are likely to include, but are not limited to, oxygen saturation, need for oxygen therapy, respiratory rate, need for ventilatory support, imaging and blood test results, amongst other clinically relevant parameters.
- Acute respiratory distress, pneumonitis, acute cardiac injury, arrhythmia, septic-shock like syndrome and acute kidney injury related with COVID-19 disease will be monitored from medical records review of hospitalised participants.
- Neurological events of >Grade 2 severity

- Eosinophilia as a marker skewed Th2 responses will be routinely monitored in participants attending their COVID-19 testing and follow-up visits. Marked eosinophilia of  $\geq 1.5 \times 10^9/L$  will be reported as an SAE.
- AEFI relevant to vaccination in general will also be monitored such as: generalised convulsion, Guillain-Barre Syndrome (GBS), Acute Disseminated Encephalomyelitis (ADEM), Thrombocytopenia, Anaphylaxis, Vasculitides in addition to serious solicited AEs will be monitored.
- (Protocol V19.0) The following conditions will be recorded as AEFIs:
  - Cerebral Venous Sinus Thrombosis
  - Heparin-Induced Thrombocytopenia
  - Major thrombosis with concurrent thrombocytopenia

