| Co-Primary | To assess the safety of the candidate vaccine ChAdOx1 nCoV-19 in adults .                               | Occurrence of serious adverse events (SAEs) throughout the study duration.                                                                                                                                                                                                                                                                                                                                                                                                 |
| Secondary  | To assess the safety, tolerability and reactogenicity profile of the candidate vaccine ChAdOx1 nCoV-19  | 
a) occurrence of solicited local reactogenicity signs and symptoms for 7 days following vaccination;
 
b) occurrence of solicited systemic reactogenicity signs and symptoms for 7 days following vaccination;
 
c) occurrence of unsolicited adverse events (AEs) for 28 days following vaccination ;
 
d) change from baseline for safety laboratory measures (except groups 4, 6, 9 and 10);
 
e) Occurrence of disease enhancement episodes
 |
|                   | To assess efficacy of the candidate ChAdOx1 nCoV-19 against severe and non-severe COVID-19              | a) Hospital admissions associated with COVID-19                                                                                                                                                                                                                                                                                                                                                                                                                            |

|  |                                                                                                                                                                        |                                                                                                                                                                                                                                                                    |

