### **7.2 Observations, medical history and physical examination**

Temperature will be routinely measured at the time-points indicated in the schedule of procedures. Respiratory rate, oxygen saturation, pulse, blood pressure and temperature will be measured at the COVID-19 testing visits and if clinically required. All subjects will undergo medical history and a targeted physical examination if considered necessary at screening or pre-enrolment on D0. The purpose of this examination is to assess and document the subject's baseline health status so that any later change can be determined. Vital signs (temperature, heart rate, respiratory rate, blood pressure +/- oxygen saturation) will be measured at screening or pre-enrolment on D0 as part of baseline assessments. Further medical history, physical examination and observations may be done throughout the study based on clinical discretion. A targeted physical examination, including neurological assessment, must be conducted, when appropriate, in the event of a SAE.

Blood tests, Nose/Throat Swabs, Saliva samples and urinalysis

Blood will be drawn for the following laboratory tests and processed at contractually agreed NHS Trust laboratories using NHS standard procedures:

- **Haematology;** Full Blood Count
- **Biochemistry;** Sodium, Potassium, Urea, Creatinine, Albumin, Liver Function Tests (ALT, ALP, Bilirubin)
- **Diagnostic serology;** HBsAg, HCV antibodies, HIV antibodies in groups 1, 2, 5a, 5b, 5c, 5d, and 5e, 5f, 7 and 8 only (specific consent will be gained prior to testing blood for these blood-borne viruses). HBsAg and HCV antibodies will be in group 12 with HIV antibodies only done at the investigators discretion.
- **Immunology;** Human Leukocyte Antigen (HLA) typing (groups 5a, 5b, 5c only)
- **COVID-19;** A nose/throat swab and/or saliva sample will be taken for COVID-19 NAAT testing.
- **CD4 count and HIV viral load;** volunteers in group 12 only, before enrolment.

Additional safety blood tests may be performed if clinically relevant at the discretion of the medically qualified investigators, including potential prognostic indicators or markers of severe COVID-19 disease

At University of Oxford research laboratories or at designated specialist laboratories:

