| Vital signs^                                                  | X   | X   | (X)     | (X) | (X) | (X) | X                |                                         |                    |                                                                |                         |
| Telephone/Video call                                          |     |     |         |     |     |     |                  | X                                       | As required        |                                                                |                         |
| Ascertainment of adverse events                               |     | X   | X       | X   | X   | X   | X                | X                                       | X                  | X                                                              | X                       |
| Diary Cards §                                      |     | X   |         |     |     |     |                  |                                         |                    |                                                                |                         |
| Weekly household exposure questionnaire                       |     |     | ongoing |     |     |     |                  |                                         |                    |                                                                |                         |
| Medical History (required at 1 timepoint prior to enrolment), | X   | X   | (X)     | (X) | (X) | (X) | (X)              | (X)                                     |                    |                                                                |                         |
| Physical Examination (if necessary)                           | (X) | (X) | (X)     | (X) | (X) | (X) | (X)              | (X)                                     |                    |                                                                |                         |
| Biochemistry, Haematology (mL)                                |     |     |         |     |     |     |                  |                                         |                    |                                                                |                         |

CONFIDENTIAL

| Attendance Number                                   | 1 | 2        | 3        | 4        | 5        | 6                  | COVID-19 Testing      | COVID-19 NAAT positive +7 days (remote) | COVID-19 Follow-up | Extra Visit A | Extra Visit B |

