#### **7.3.4.2 COVID-19 testing visit**

Participants will be invited for a COVID-19 testing visit in two circumstances:

- They report primary endpoint symptoms AND have not already had a documented negative SARS-CoV-2 NAAT test result (including trial weekly swabs and tests performed outside of the trial) since their symptom onset
- They report primary endpoint symptoms and have had a positive SARS-CoV-2 NAAT test from their trial weekly swab test or from outside of the trial since symptom onset

At the COVID-19 testing visit, a nose/throat and immunology bloods (paxgenes, cytokine profile, PBMCs, serum and others, according to local site capacity) will be acquired. Clinical assessments may be performed at COVID-19 testing visits at the discretion of investigators. Symptomatic volunteers may be regularly reviewed over the phone or via video call using a smartphone or computer app if clinically appropriate. Participants who have a positive NAAT will be reviewed by phone for symptom severity data at approximately 7 days post positive swab. Closer follow-up and safety monitoring may be carried out by local trial teams if felt this is clinically indicated. Symptomatic participants with a positive NAAT test outside of the trial or as part of their trial weekly swab tests will be asked to attend for a COVID-19 testing visit in order to take a further swab to facilitate SARS-CoV-2 sequencing and additionally to acquire immunology bloods.

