#### **7.3.4.3 COVID-19 Testing plus 7 day phone call**

For symptomatic participants with a positive SARS-CoV-2 NAAT test, a remote follow up (via phone or other appropriate means) will take place at approximately 7 days (see schedule of procedure tables for window, section **Error! Reference source not found.**) from the date of their first positive NAAT test in that illness episode. The purpose of this remote follow up is to capture further symptom severity data.

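### Section 9.4 says eosinophilia is routinely monitored at COVID-19 visits, but no randomised group has a blood count scheduled there, so absence of reported eosinophilia is not a negative finding

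*Protocol*

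**What the plan says.** Section 9.4 (Adverse Events of Special Interest) states, with no restriction by group: "Eosinophilia as a marker skewed Th2 responses will be routinely monitored in participants attending their COVID-19 testing and follow-up visits". It adds that marked eosinophilia, 1.5 x 10^9/L or more, "will be reported as an SAE". Such events therefore enter the co-primary safety outcome, "Occurrence of serious adverse events (SAEs) throughout the study duration".

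An eosinophil count comes from the haematology test, which section 7.2 defines as "Full Blood Count".

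For the COVID-19 visits themselves, section 7.3.4.2 says: "At the COVID-19 testing visit, a nose/throat and immunology bloods (paxgenes, cytokine profile, PBMCs, serum and others, according to local site capacity) will be acquired". Section 7.3.4.3 makes the contact at about seven days remote and gives its purpose: "The purpose of this remote follow up is to capture further symptom severity data".

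In Tables 4 to 12 the haematology row is blank at COVID-19 testing, at the +7 day contact and at COVID-19 follow-up. Table 13 (group 12) schedules 5 mL of haematology at COVID-19 testing and again at +7 days.

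**The concern.** The protocol states a safety-monitoring property that its schedule does not deliver in any randomised group. Someone reading section 9.4 alone would suppose that every participant attending a COVID-19 visit had an eosinophil count, and that a table showing no marked eosinophilia was a measured result. In most groups no such measurement is planned.

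The one group with scheduled counts has no comparator, so scheduled data cannot support a vaccine-versus-control comparison of eosinophilia. Any counts in the randomised groups would come from tests ordered when judged clinically relevant (section 7.2) or from notes on medically attended episodes (section 7.5). Both routes plausibly favour sicker participants. If the vaccine changes severity, the chance of being tested could then differ by arm. The documents do not say this; it is an inference from how those counts arise.

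**Working it through.** **Step 1: are the blank cells real?** Tables can lose entries in conversion from PDF, so I checked the blanks against the blood volumes. At the COVID-19 testing visit:

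volume = exploratory immunology + PAXgene + haematology (if scheduled)

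The result is compared with the printed per-visit volume and with the step in the cumulative row. All figures are in mL.

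| Table | Groups | Sum of filled rows | Printed | Cumulative step |
|---|---|---|---|---|
| 4 | 1a, 2a, 7a, 8a | 50 + 2.5 = 52.5 | 52.5 | 440 - 387.5 = 52.5 |
| 5 | 1b, 2b, 5d, 7b, 8b | 50 + 2.5 = 52.5 | 52.5 | 555 - 502.5 = 52.5 |
| 6 | 5e, 5f | 50 + 2.5 = 52.5 | 52.5 | 625 - 572.5 = 52.5 |
| 7 | 4a, 6a | 50 + 2.5 = 52.5 | 55.5 | 307.5 - 255 = 52.5 |
| 8 | 4b | 50 + 2.5 = 52.5 | 52.5 | 407.5 - 355 = 52.5 |
| 9 | 5a1, 5a2, 5b, 5c | 50 + 2.5 = 52.5 | 52.5 | 444 - 391.5 = 52.5 |
| 10 | boosters, incl. 4c and 6b | 50 + 2.5 = 52.5 | 52.5 | 302.5 - 250 = 52.5 |
| 11 | 9, 10 | 50 + 2.5 = 52.5 | 52.5 | 352.5 - 300 = 52.5 |
| 12 | 11 | 50 + 2.5 = 52.5 | 52.5 | 405 - 352.5 = 52.5 |
| 13 | 12 | 95 + 5 + 2.5 = 102.5 | 102.5 | 1030 - 927.5 = 102.5 |

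A 5 mL haematology sample would bring Tables 4 to 12 to 57.5 mL, and none shows that. Table 7 prints 55.5, but its own cumulative row moves by 52.5. That is a separate small discrepancy and does not indicate a blood count. Table 13 balances only with the haematology sample included. The blanks are therefore real.

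**Step 2: could a count be taken at follow-up instead?** Outside group 12 the +7 day contact is remote in both section 7.3.4.3 and the tables, with no blood entry. Further COVID-19 follow-up is a telephone or video call as required. For group 12, Table 13 schedules bloods at +7 days, while section 7.3.4.3 makes that contact remote with no exception for the group. The one schedule that contains the test thus also conflicts with the text.

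**Step 3: who has a scheduled count?** Group 12 is up to 60 people: 60 / 12,390 = 0.48%. The listed group sizes sum to 80 + 120 + 3,550 + 290 + 6,000 + 80 + 120 + 1,000 + 1,000 + 60 + 60 = 12,360, slightly below the stated maximum; the share is 0.5% on either total. Groups 4, 6, 9 and 10 have no haematology at any scheduled visit in Tables 7, 8, 10 and 11. They number 3,550 + 6,000 + 1,000 + 1,000 = 11,550, and 11,550 / 12,360 = 93%.

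These shares are of participants. The protocol gives no number of COVID-19 testing attendances, so the share of episodes without a count cannot be computed from it.

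**The case against.** **Other sources of counts.** Section 7.2 allows additional safety bloods at the investigator's discretion, including markers of severe COVID-19, and section 7.5 provides for notes review. The amendment log for version 18.0 also suggests that safety bloods may have been taken at these visits under earlier versions. A reader might infer that a reported zero would simply mean eosinophilia was not measured. The documents do not support that: some episodes may well have a count. What stands is that those counts are not routine in the current text and that measured and unmeasured episodes would be mixed.

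**The open-ended list in 7.3.4.2.** The list there ends with unnamed others, which might be said to cover a blood count. It describes immunology bloods, subject to site capacity. Section 7.2 assigns haematology to NHS laboratories and immunology to research or specialist laboratories, and the schedules give them separate rows. This reading fails.

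**Disease enhancement.** A reader might infer that eosinophilia is the stated marker of disease enhancement, so that no conclusion on enhancement is possible without a blood count. Section 9.4 calls it a marker of skewed Th2 responses only. Disease enhancement has its own entry, based on clinical criteria and medical records, and does not depend on this test.

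**Analysis detail and timing.** Denominators commonly belong in the statistical analysis plan, and their absence from the protocol is not criticised here. The reporting request follows from the contradiction. At this version the primary efficacy analysis is complete, all participants are to be unblinded and group holding rules no longer apply. That lowers the operational stakes but does not change what an absence of eosinophilia can be taken to show.

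**Conclusion.** The contradiction holds. Section 9.4 promises routine eosinophil monitoring at COVID-19 testing and follow-up visits, but the visit text and Tables 4 to 12 schedule no test that could provide it. Scheduled counts exist only in group 12: at most 60 of up to 12,390 participants (0.5%), with no control arm. About 93% of planned participants are in groups with no scheduled haematology at all.

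Absence of reported eosinophilia in the randomised groups therefore cannot be read as a negative finding. The conclusion rests on the full blood count being the source of an eosinophil count, as section 7.2 implies, and on the schedules being followed as printed. It does not rest on the amendment log or on any assumed difference in testing between arms. It concerns eosinophilia only and leaves the assessment of disease enhancement as it is.

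**What to change.** Reconcile section 9.4 with sections 7.3.4.2 and 7.3.4.3 and with Tables 4 to 13, including the group 12 conflict at +7 days. Whether the monitoring statement or the schedule changes is for the sponsor.

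In either case, specify for the safety analysis that:

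- eosinophilia is reported by arm, over COVID-19 episodes that had a blood count;
- the number of episodes without a count is shown beside it, also by arm;
- no conclusion about eosinophilia is drawn from episodes without a count.

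**Cost.** The reporting change adds one denominator to a safety table and gives a less reassuring statement. Changing the wording of section 9.4 costs little beyond the amendment. Keeping it as written costs more. A reader might suppose that one tube from blood already being drawn would do, but exploratory blood at the testing visit is marked optional and subject to site capacity in Tables 7, 8, 10, 11 and 12. With the 5 mL sample used elsewhere in the schedules, the visit would rise from 52.5 to 57.5 mL, and counts at follow-up would need in-person contact in place of the remote one.

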## 9.5 Causality

For every AE, an assessment of the relationship of the event to the administration of the vaccine will be undertaken by the CI-delegated clinician. An interpretation of the causal relationship of the intervention to the AE in question will be made, based on the type of event; the relationship of the event to the time of vaccine administration; and the known biology of the vaccine therapy (Table 13). Alternative causes of the AE, such as the natural history of pre-existing medical conditions, concomitant therapy, other risk factors and the temporal relationship of the event to vaccination will be considered and investigated. Causality assessment will take place during planned safety reviews, interim analyses (e.g. if a holding or stopping rule is activated) and at the final safety analysis, except for SAEs, which should be assigned by the reporting investigator, immediately, as described in SOP OVC005 Safety Reporting for CTIMPs.

|   |                        |                                                                                                                                                                                                              |
|---|------------------------|--------------------------------------------------------------------------------------------------------------------------------------------------------------------------------------------------------------|
| 0 | No Relationship | No temporal relationship to study product and
Alternate aetiology (clinical state, environmental or other interventions); and
Does not follow known pattern of response to study product |
|---|------------------------|--------------------------------------------------------------------------------------------------------------------------------------------------------------------------------------------------------------|

|   |                 |                                                                                                                                                                                                                                                |
|---|-----------------|------------------------------------------------------------------------------------------------------------------------------------------------------------------------------------------------------------------------------------------------|
| 1 | Unlikely | Unlikely temporal relationship to study product and
Alternate aetiology likely (clinical state, environmental or other interventions) and
Does not follow known typical or plausible pattern of response to study product. |
| 2 | Possible | Reasonable temporal relationship to study product; or
Event not readily produced by clinical state, environmental or other interventions; or
Similar pattern of response to that seen with other vaccines                  |
| 3 | Probable | Reasonable temporal relationship to study product; and
Event not readily produced by clinical state, environment, or other interventions or
Known pattern of response seen with other vaccines                             |
| 4 | Definite | Reasonable temporal relationship to study product; and
Event not readily produced by clinical state, environment, or other interventions; and
Known pattern of response seen with other vaccines                           |

Table 15. Guidelines for assessing the relationship of vaccine administration to an AE.

